# STUDY DESIGN/METHODOLOGY

The protocol presented is based on both the Standard Protocol Items: Recommendations For Interventional Trials (SPIRIT) (2013) and Consolidated Standards of Reporting Trials (CONSORT) (2018) guidelines, to conduct an acceptability and feasibility pilot study. The proposed protocol is for a new intervention. There have been no previous trials using the MyoMunchee
[figure not shown]
 (a myofunctional device) in the area of oral hygiene and dysphagia with those in an aged care setting. A cluster randomised control trial in Sweden by Hagglund and colleagues (2019) utilised a myofunctional device (used for promoting lip closure and nasal breathing) for oral neuromuscular training for those 65 years and older in short term care units with impaired swallowing. Hagglund and colleagues (2019) study indicated that swallowing function significantly improved for those in the intervention group immediately following 5 weeks of therapy with the use of the myofunctional device, and a significant reduction in signs of aspiration compared to the control group 6 months post treatment.

The use of this study will provide important information regarding the feasibility and efficacy of a new treatment for oral hygiene and dysphagia with the MyoMunchee
[figure not shown]
, and provide information for calculating the sample size needed for a randomised control trial (In, 2017, & Eldridge, et al., 2016). Thabane and Lancaster (2019), In (2017), and Eldridge, et al., (2016) highlight the importance of feasibility studies to further guide and inform conduct and design of a larger clinical trial or future research.

The feasibility of the treatment intervention will be measured by way of:

- Verbal survey of the residents receiving the intervention regarding experience using the device, using a 5-point Likert scale (very difficult – very easy), and dichotomous questions (yes – no) (Appendix A).
- Questionnaire for care staff (nursing/allied health) in the implementation and acceptability of assisting participants with the myofunctional device, using both a 5-point Likert scale (very difficult – very easy), dichotomous questions (yes – no), and free text (Appendix B).
- The consenting rates,
- Treatment completion rates,
- Treatment adherence (which will be monitored on the daily check list provided by care staff, see Appendix C, D, E, F, G).

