# STUDY OUTCOMES

1. **Quantitative**
2. **Primary Outcome**

Feasibility and acceptability of treatment intervention. This will include the number of participants approached versus consented, completed treatment rates, and adherence to the intervention (monitored by care staff with supervision of the intervention, and completion of daily intervention sheets).

1. **Secondary Outcome(s)**

Secondary outcome measures will be collected both pre and post intervention, and are outlined in Table 1.

**Table 1** Secondary outcome measures for collection pre and post intervention

| Outcome Measure | Reference | Outcome | Description |
| --- | --- | --- | --- |
| Oral Health Assessment Tool (OHAT) | [6] | Oral health | Reliable and valid screening tool for use in aged care and with cognitive impairment; Approximately 7-8 minutes to administer; 8 items, Rating scale – 0 = healthy, 1 = changes, 2 = unhealthy; Total score out of 16, The higher the score the worse the oral health; Items that score 1 indicate intervention is required, and items scoring 2 indicate referral to a dental professional is required |
| Timed Water Swallow Test (WST) | [18] | Aspiration risk | Swallow speed is a sensitive indicator for identifying patients at risk of swallow dysfunction; Choking in 100ml WST may be a potential indicator for follow up aspiration; Measures swallow time, number of swallows and observes for signs of choking; Abnormal swallow is defined as a speed below 10ml/s (amount of water divided by elapsed time); Count the number of swallows taken to consume 100mls water; Time taken to consume 100mls water |
| Test of Mastication and Swallowing Solids (TOMASS) | [17] | Mastication ability | Quantitative assessment of solid bolus ingestion; Sensitive in detecting changes in performance ability of mastication; High interrater and test-retest reliability; Count number of bites, number of masticatory cycles per bite, number of swallows per bite; More likely to identify patients with subtle oral phase impairment or bolus transition issues; Normative ranges in older adults: number of bites (male 1.47/female 1.87), time in seconds (male 32.61/female 41.85), total number of swallows (male 3.61/female 3.5), masticatory cycle (male 37.6/female 41.65) |

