| Mann Assessment of Swallowing Ability (MASA) | [24] | Identify swallowing disorders | Screening bedside tool to identify eating and swallow disorders in stroke and other diseases; Used to quantify aspiration risk; 24 clinical items; 4 components of the assessment include, general patient examination, oral preparation, oral phase, and the pharyngeal phase; 5-10 point rating scale; score out of /200, >178 = normal, 168-177 = mild, 139-167 = moderate, <138 = severe; risk of aspiration is defined on a sum of the 4 scores/categories, >170 = normal, 149-169 = mild, 141-148 = moderate, <140 = severe |
| Functional Oral Intake Scale (FOIS) | [8] | Functionality | 7 point ordinal scale; Functional level of oral intake of food and liquid; Interrater reliability high and sensitive to changes; Levels 1-3 relate to non-oral feeding; Levels 4-7 relate to varying degrees of oral feeding; All levels focus on what is/not consumed orally |
| Eating Assessment Tool (EAT-10) | [4] | Self-perceived symptoms | Screen self-perceived oropharyngeal dysphagia symptoms; Scores range from 0-40; Scores >3 are indicative of dysphagia; 10 questions rated on a 5 point scale, 0 = no problem, 4 = severe problem; Scores >15 indicative of aspiration risk; An elevated EAT-10 score indicates a higher self-perception of dysphagia |
| Mini Mental State Examination (MMSE) | [26] | Cognitive function | Widely used screening test of mental function; Evaluates cognitive impairment in older adults; 10 minutes to complete; normal = 30-25, mild = 24-21, moderate = 21-10, severe = 9-0 |

1. **Qualitative**
2. Administer Care Staff Acceptability Questionnaire to those assisting with the intervention/observing the use of the myofunctional device to rate the ease of use and cleaning of the device, the impact on workload, and perceived acceptance by residents.

Administer a Resident Acceptability Survey to all enrolled residents, regarding ease of use, comfort with use, and if there were perceived changes to oral health or swallowing following the use of the device. Assistance in reading the survey to those residents with visual impairment, aphasia, and cognitive and intellectual impairment will be provided by the care staff.

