) will be used twice daily (morning and evening recommended at the time of usual oral care routine) by the participants. The duration for device use will start at 1 minute twice a day in the first week, and increase to 2 minutes twice a day in the second week, 3 minutes twice a day in the third week, 4 minutes twice a day in the fourth week, and 5 minutes twice a day use in the fifth week of intervention.

Following the five week trial of intervention, post-treatment outcome measures will be taken by the lead researcher from the University of Newcastle.

Post treatment intervention, residents will be asked to take part in a survey regarding the acceptability of the myofunctional devices.

Protocol Flow:

1. **Methods of data collection**

Data collection will be completed by a qualified clinical speech pathologist/principal investigator (with over 17 years clinical experience) with reliability checking of 10% of residents onsite at Maroba Aged Care by a qualified clinical speech pathologist from the University of Newcastle.

Pre and post treatment outcome measures will be taken for comparison, along with data collected for adherence to treatment by way of daily checklist completion by the care staff, which will be collected at the end of each week and stored by the research team for the duration of the trial. Further to this a survey of the residents completing the intervention, as well as a questionnaire for the care staff assisting participants with the intervention will be taken at the completion of the five week intervention trial.

1. **Access to Existing Data**

Data (as per the form below) will be extracted from the medical files of each consenting participant by an employee appointed by Maroba Aged Care. The data will be deidentified using a code and then provided to the research team.

| **Name/Description of data** | **Myofunctional Devices Research** | | | | |
| --- | --- | --- | --- | --- | --- |
| **Data Custodian** | University of Newcastle | | | | |
| **Agency Type** | Higher Education | | | | |
| **Data Collection Format** | Non-identifiable | | | | |
| ***Variable*** | ***Justification*** | | | | |
| **Resident ID number** |  | | | | |
| **Male/Female/Non-binary** |  | | | | |
| **Date of Birth/age** |  | | | | |
| **Identifies as Aboriginal or Torres Strait Islander** | Yes/No | | | | |

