# ETHICAL CONSIDERATIONS

All eligible and consented participants will be informed of the potential risks and proposed benefits of the study procedures, the priority of the participants’ interests over those of science or of society.

The Myofunctional Device (MyoMunchee
[figure not shown]
) has been approved by the Australian Government Department of Health (2019), Therapeutic Goods Administration as a medical device class 1 (low risk device), with intended purpose to exercise the jaw and surrounding muscles, as well as other conditions treated by oral motor therapy. The myofunctional device (MyoMunchee
[figure not shown]
) is ISO 13485 certified by the Standard for Quality Management System for design and manufacturing of medical devices, and is made of non-toxic medical grade silicone.

1. **Vulnerable populations**

This study will involve vulnerable populations, including the elderly and those with chronic health conditions (including cognitive difficulties such as dementia). Informed consent will be obtained from residents/family members of residents if resident unable to provide consent/care staff to take part in this research. Residents/family members of residents/care staff will be required to read and understand the information (Participant Information Statement (PIS)) provided by the research team they need to make an informed decision about their voluntary participation. There will be allowances made for those who cannot read but would like to participate and the PIS can be read to them. Participants/family members of participants who consent to the intervention are permitted to change their mind and withdraw from participation at any time during the study.

1. **Confidentiality**

Confidentiality of all records is guaranteed and no information by which a person can be identified will be released and only anonymous data will be published. Participants will be assigned a pseudonym for the purposes of presentation/further dissemination of the research in order to protect their privacy and confidentiality. All files will be password protected and only accessible by the research team at the University of Newcastle.

1. **Ethical Review**

The study will be conducted in full conformance with principles of the National Statement on Ethical Conduct in Human Research (NHMRC, 2007), Australian Code for the Responsible Conduct of Research (2007) and within the laws and regulations Australia.

Ethical approval will be sought from the following:

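### The protocol gives the resident acceptability survey to all enrolled residents in one section and to those completing the intervention in another; read literally, the second leaves out residents who stop early

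*Protocol*

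**What the plan says.** The protocol describes who receives the resident survey in four places.

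- Study Design/Methodology, first item in the list of feasibility measures: "Verbal survey of the residents receiving the intervention regarding experience using the device".
- Study Outcomes, Qualitative: "Administer a Resident Acceptability Survey to all enrolled residents".
- Study Procedures, description of the resident procedures: "Post treatment intervention, residents will be asked to take part in a survey regarding the acceptability of the myofunctional devices".
- Study Procedures, Methods of data collection: "Further to this a survey of the residents completing the intervention", which, with the staff questionnaire, "will be taken at the completion of the five week intervention trial".

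The primary outcome in Study Outcomes is headed "Feasibility and acceptability of treatment intervention". The components listed under it are the numbers approached and consented, "completed treatment rates, and adherence to the intervention". The Ethical Considerations section says that participants or their families "are permitted to change their mind and withdraw from participation at any time during the study". The safety monitoring text under Study Procedures separately provides for discontinuing the intervention in an individual.

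**The concern.** The survey asks about ease of use, comfort, and any change that the resident noticed. The residents best placed to report poor comfort or difficulty are those who stopped because of it. If staff follow the methods of data collection as written, these residents are not approached: they have not completed the intervention, and the only time given is the end of the five weeks.

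The ratings would then depend on having found the device tolerable enough to finish. The study is meant to inform a larger trial, and Study Procedures says that the larger trial may not go ahead, depending on these results. A survey that leaves out early stoppers weakens one of the sources for that decision. It also cannot be repaired at analysis, because a rating not collected when a resident stops may not be recoverable later.

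**Working it through.** **Step 1. Set the survey populations side by side.**

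| Place in the protocol | Who is surveyed | When |
| --- | --- | --- |
| Study Design/Methodology | residents receiving the intervention | not stated |
| Study Outcomes, Qualitative | all enrolled residents | not stated |
| Study Procedures, resident procedures | residents, unqualified | after treatment |
| Study Procedures, Methods of data collection | residents completing the intervention | completion of the five weeks |

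**Step 2. See which of these really differ.** Study Procedures says that all consented residents will be treated. Enrolled and receiving the intervention are therefore nearly the same group. They part only for a resident lost between baseline assessment and first use of the device, an interval of up to two weeks. The third wording sets no limit on who is asked. The conflict is between these broader wordings and the fourth.

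**Step 3. See whether the difference can matter.** The groups coincide only if everyone who starts also finishes. The protocol does not assume this: completion is one of its outcomes, and withdrawal and discontinuation are provided for. Nothing in the document as shown sets a survey time for a resident who stops early.

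**Step 4. Illustrate the size.** The protocol states no dropout rate and no expected rating, so there is no figure of its own to reproduce. All inputs here are assumed, except the 50, which is the upper recruitment target for residents.

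Assume that 50 start, 15 stop early, and 28 of the 35 completers rate the device favourably.

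- Completers only: 28/35 = 80% (exact 95% CI 63% to 92%).
- All starters, no stopper favourable: 28/50 = 56% (exact 95% CI 41% to 70%).
- All starters, every stopper favourable: (28 + 15)/50 = 86%.
- Break-even: 80% of 15 is 12. The completer figure is too high if fewer than 12 of the 15 stoppers are favourable, and too low if more than 12 are.

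**Step 5. Vary the completion rate.** Let c be the proportion completing. Overall acceptability = c × (rate in completers) + (1 − c) × (rate in stoppers). Assume 80% in completers and 20% in stoppers.

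| Completion c | Not asked, of 50 | Overall | Completers only | Difference |
| --- | --- | --- | --- | --- |
| 90% | 5 | 0.9 × 80 + 0.1 × 20 = 74% | 80% | 6 points |
| 80% | 10 | 0.8 × 80 + 0.2 × 20 = 68% | 80% | 12 points |
| 70% | 15 | 0.7 × 80 + 0.3 × 20 = 62% | 80% | 18 points |
| 60% | 20 | 0.6 × 80 + 0.4 × 20 = 56% | 80% | 24 points |

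Step 5 builds in lower ratings among stoppers. It shows how the gap grows with dropout, not that there is a gap.

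**The case against.** The strongest reply is that the restriction rests on one participle. Completing can mean carrying out, and the protocol uses completion in that sense when it speaks of daily monitoring and of the twice-daily sessions. Read so, the four wordings agree. This reading is possible. But the protocol also uses completion for finishing treatment, in its completion rates, and the sentence in question places the survey at the end of the five weeks. Even on the looser reading, early stoppers have no stated survey time.

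Second, those who stop are not invisible. They lower the completion and adherence figures, reported discomfort triggers a review, and staff are asked how well residents seemed to accept the device. This stands, and it makes it less likely that poor acceptance would go unnoticed. It does not supply the rating of a resident who stopped.

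Three stronger readings are tempting, and the document does not support them.

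- A reader might infer three distinct survey populations. Because all consented residents are to be treated, there are in practice two.
- A reader might infer that the survey result is itself a listed primary endpoint. Acceptability is in the primary outcome heading and the survey is listed as a feasibility measure, but the components named under the heading are consent, completion and adherence. The survey is detailed under Qualitative and its responses go to content analysis. No headline percentage is planned.
- A reader might infer that the bias is certainly upward. The 56% to 86% range contains the completer figure of 80%, so the direction is likely but not proven.

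Finally, the flow chart and the survey form are not in the text available for this review, and either may say who is asked and when.

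**Conclusion.** The inconsistency is real and lies in current text. Followed literally, the methods of data collection leave out enrolled residents who stop early, and the residents' own acceptability ratings would probably, though not certainly, be too favourable. That direction rests on the assumption that residents who stop rate the device lower than those who finish. The size cannot be fixed from the protocol. On the assumed rates of 80% and 20%, the overstatement runs from 6 points at 90% completion to 24 points at 60%.

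The point concerns only enrolled residents who began using the device. Those who decline consent are outside every version of the survey, and the pre-post efficacy measures are a separate matter. It should be corrected, because it decides whom staff approach and when, and an analysis plan cannot recover ratings that were never collected.

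**What to change.** Align the sentence under Methods of data collection with Study Outcomes and Study Design/Methodology, so that all say the same thing: every enrolled resident who started the device is offered the survey. State the timing: at the end of week 5 or, for a resident who stops early and is willing, at or soon after stopping. Make the unqualified sentence in the resident procedures agree.

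Report the ratings with the number who started as denominator, show non-responders as their own category, and give the completer results second.

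The cost is a few wording changes and giving the existing short survey earlier to those who stop. Some of them may decline, as the right to withdraw allows, and they would then appear as non-responders.

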**Inclusion criteria**

1. age > 65 years

2. Ability to understand English and follow instructions for timed water swallow test and use of the myofunctional device

3. Residents receiving texture modified diets and/or fluids

4. Residents with natural teeth, dentures (partial and full), and edentulous

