Staff:

Education will be provided before the commencement of the trial intervention by the principal investigator from the University of Newcastle to care staff, regarding familiarization and instructions for use of the myofunctional device (MyoMunchee
[figure not shown]
), cleaning and storage of the device, and documentation of device use.

The use of a myofunctional device (MyoMunchee
[figure not shown]
) will be required for each participant for the duration of this intervention and will be provided in kind by MyoMunchee
[figure not shown]
. Further explanation regarding the cleaning, cleaning schedule and storage of this will be provided in the treatment protocol as per MyoMunchee
[figure not shown]
 cleaning protocol.

The research team will provide the residents/care staff with instructions and a guide for the use of the device. This will require active use of the device with the action of chewing.

The use of the myofunctional device will be monitored by the care staff at Maroba Aged Care, with documentation on a daily checklist provided for each participant. The daily checklist will be collected by the care staff at Maroba Aged Care at the end of each week of intervention and entered into an electronic database each week by the principal investigator.

Following the five week intervention, the care staff will be asked to complete a questionnaire regarding acceptability and feasibility of the trial intervention.

Residents:

Once participants who meet the selection criteria are enrolled in the study, outcome measures will be collected and stored by the principal investigator from the University of Newcastle. The collection of outcome measure should take approximately 60 minutes for each participant.

There will not be any alteration to the participant’s usual intervention for oral care or swallowing treatment unless this is deemed appropriate by the usual treating speech pathologist/s at Maroba Aged Care, or the treating medical/nursing team.

The trial intervention using the myofunctional device will commence within two weeks post pre-treatment outcome measure collection.

The myofunctional device (MyoMunchee
[figure not shown]

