| **Underlying Medical Diagnosis** | - CVA– year _________________ - Dementia - Parkinson’s Disease - Cardiovascular disease - Cancer – specify _____________ - COPD - Diabetes - Multiple Sclerosis - Epilepsy | | | - Hypertension - Osteoporosis - Arthritis - Depression - Asthma - Motor Neuron Disorder - Polymyositis - Other_______________________   ___________________________ | |
| **Dentition (own, edentulous, dentures)** | Own/Dentures/Edentulous | | | | |
| **Diet/Fluid consistency** | - NBM - PEG - JJ Tube - Other _________ | - Liquidized - Puree - Minced Moist - Soft Bite Sized - Easy Chew - Normal Diet | | | - Extremely Thick - Moderately Thick - Mildly Thick - Slightly Thick - Thin fluids |
| **MMSE score/date last assessment** | Score: | | Date: | | |
| **Independence in oral care** | Yes/no/maybe/unsure | | | | |
| **Living status** | Independent living/ACF (check terminology) | | | | |

1. **Safety considerations**

This study involves a new intervention with a vulnerable population. However, the intervention uses a device that has Therapeutic Goods Approval and the residents who will be using this device will be monitored by care staff during the intervention.

Potential Risks and Solutions for residents undertaking intervention

| **Potential Risks** | **Solutions** |
| --- | --- |
| Aspiration of saliva secondary to increased saliva production during device use | Aspiration of saliva occurs daily. The continued use of usual oral care during this study to ensure adequate oral hygiene should assist with reducing complications that may arise from aspiration of saliva  Monitoring by care staff to ensure participants have adequate salvia management/control  If coughing occurs through use of the device and increased saliva production, a referral will be made for speech pathology at Maroba to review swallowing function (and appropriateness for continuation in study) |
| Initial discomfort to gums/jaw with the action of chewing the device | The treatment intervention has been staged in time use of the device, increasing weekly to allow for adjustment to oral comfort. If oral discomfort is identified/reported, a review by the researcher and speech pathologist at Maroba Aged care will take place and recommendations will be made for continuation in the study.  Sizing and selection of the device has been considered for oral comfort and ease placing and removing the device from the oral cavity with an eternal tab/handle. |

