| Infection control | Infection control procedures are outlined in the treatment manual and are consistent with Covid 19 safety and cleaning measures. Staff will be trained in cleaning protocols for the device (which are not aerosol generated) to reduce the risk of infection. Daily cleaning will be tracked with the completion of a daily check list by care staff at the ACF. |

The risks to the participants undertaking intervention is considered negligible to low risk. There is low foreseeable risk of harm or discomfort, and any foreseeable risk is no more than an inconvenience (National Statement on Ethical Conduct in Human Research, 2007).

There are no known risks for the care staff assisting with the intervention outside of usual oral care assistance.

Further considerations have been made below not specifically to risk, but rather in regard to storage and labelling, which may impact on infection control for the use of the device.

Device considerations and storage

| Potential Concern | Strategy |
| --- | --- |
| Device labelling/identification | Devices will be stored as per dentures in storage container specifically for the MyoMunchee, labelled with the participants identification number.  The MyoMunchee will be stored as per Maroba Aged Care protocol for storage and identification of usual oral hygiene products |
| Lost/misplaced device | In the event of the MyoMunchee being misplaced/lost a new replacement device will be provided |

1. **Data monitoring for safety**

Data monitoring will occur throughout the study for the safety of residents undergoing the intervention by way of:

- Pre and post intervention assessment
- During intervention with daily monitoring of completion of the trial intervention and completion of data sheets by care staff
- Weekly collection of data sheets to ensure no adverse events

Monitoring and reporting of adverse events (AE), serious adverse events (SAE) and unexpected events (UE) will be conducted as per Maroba Aged Care incident reporting system ‘ionMY’ (governance, risk management, compliance platform), and entered by care staff as per Maroba Aged Care incident reporting guidelines. Events will be reported to the principal investigator within 24 hours of the UE/AE/SAE and entered into the University of Newcastle adverse events form in Research Information Management System within 72 hours of being reported as per NHMRC (2016) guidelines.

All UE/AE/SAE will be:

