- assessed by the principal investigator using the University of Newcastle risk assessment matrix and NHMRC (2016) guidelines of level of severity

Grading system for AE

| **Level of severity** | **Criteria of level of severity** |
| --- | --- |
| Mild | Requires minimal/no treatment and do not interfere with daily activities |
| Moderate | Results in low level inconvenience or concern. May cause some interference with function |
| Severe | Interrupts usual daily activity and may require other treatment |

- Reported to the sponsor and trial site by the principal investigator within 24 hours of the principal investigator becoming aware of any urgent safety concerns

Discontinuation of intervention for a participant may occur if:

- There is an AE or medical condition that occurs such that participation in the study would not be in the best interest of the participant
- The participant met an exclusion criterion (newly developed of not identified on consent) that precludes further study participation

Care staff who have concerns that a participant is no longer suitable to continue the intervention will be able to contact the principal investigator both during work hours and after hours via phone/email provided.

1. **Protocol Deviations**

Acknowledgment of the completion of twice daily intervention with the MyoMunchee will be confirmed by care staff via a checklist provided. The checklist will be collected by care staff at the end of each intervention week and replaced with a new intervention checklist with instructions for the intervention for that week.

Deviations from the study protocol such as the use of the device or adherence of the participant or the study site staff will be addressed by the principal investigator. The principal investigator will use continuous vigilance to identify and report deviations within 72 hours of identification of the protocol deviation.

1. **Unexpected or Serious Adverse Events**

The study procedures are not greater than minimal risk, and serious adverse events (SAE) are not expected.

- AE’s are those resulting in any untoward medical occurrence as a result of the intervention
- SAE’s are those resulting in death, life threatening AE’s, requiring hospitalization, or significant disruption of ability to conduct normal functions

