- UE’s are those incidents/experiences that warrant consideration of change to the intervention protocol for the safety and welfare of the participant (National Health and Medical Research Council (2016).

The principal investigator will use continuous vigilance to identify and report adverse events within 72 hours of identification of the event to all approving relevant parties.

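### The adverse event definition requires causation by the intervention, so it leaves out non-serious events judged unrelated to the device and harm from the study's own swallow tests

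*Protocol*

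**What the plan says.** Under Study Procedures, Unexpected or Serious Adverse Events, the protocol gives three definitions.

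- Adverse events (AEs) are "those resulting in any untoward medical occurrence as a result of the intervention".
- Serious adverse events (SAEs) are listed by consequence: death, life-threatening AEs, and events "requiring hospitalization, or significant disruption of ability to conduct normal functions".
- Unexpected events (UEs) are "those incidents/experiences that warrant consideration of change to the intervention protocol for the safety and welfare of the participant".

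Data monitoring for safety sends all three through the facility's incident system, "entered by care staff as per Maroba Aged Care incident reporting guidelines". They are then reported to the principal investigator, who grades them with a university risk matrix and national guidance on severity. The same subsection names the pre- and post-intervention assessments among its safety-monitoring points.

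On timing, the Study procedures subsection says: "The trial intervention using the myofunctional device will commence within two weeks post pre-treatment outcome measure collection". The water and solid-bolus swallow tests appear in Study Outcomes, Table 1, as outcome measures taken before and after treatment.

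**The concern.** An AE definition normally takes in every untoward occurrence and treats causation as a second, separate judgement. Here causation is the entry condition, and the protocol does not say who judges it or by what method.

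That matters more than usual in this study for three reasons.

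- The population is already prone to the event of interest. Inclusion criterion 3 is "Residents receiving texture modified diets and/or fluids", and the Background rests on the link between poor oral health and aspiration pneumonia.
- The risk table names "Aspiration of saliva secondary to increased saliva production during device use" as a potential harm of the device. A respiratory infection could therefore come from the device or from the resident's existing condition.
- All consented residents receive the device and nobody is randomised, so no comparison group exists from which to correct a doubtful individual attribution.

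The study also imposes its own hazard. Residents on modified diets or fluids are asked to drink 100 ml of water against the clock and to eat a solid bolus. Table 1 acknowledges the first: "Choking in 100ml WST may be a potential indicator for follow up aspiration". At stake is whether the study's AE record includes the non-serious events that a reader would look for first.

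**Working it through.** No arithmetic settles this point, and no figure in the protocol bears on it. The check sets the definitions against the events they have to classify.

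**Step 1: what intervention means.** The Study procedures subsection uses the word for the five-week device programme. It begins up to two weeks after the pre-treatment measures. The swallow tests are outcome measures and are nowhere described as part of the intervention.

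**Step 2: apply the three definitions.**

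| Event | AE line | SAE line | UE line |
| --- | --- | --- | --- |
| Chest infection, treated on site, judged not due to the device | Excluded | Only if it significantly disrupts normal function | Only if it prompts thought of changing the intervention protocol |
| Chest infection, hospitalised or fatal, judged not due to the device | Excluded | Included on a literal reading; excluded if SAEs are a subset of AEs | As above |
| Choking or aspiration in the baseline swallow tests | Excluded: the intervention has not begun | Only if a seriousness criterion is met | As above |
| Choking or aspiration in the post-treatment swallow tests | Excluded unless traced to the device | Only if a seriousness criterion is met | As above |

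**Step 3: look for a broader rule elsewhere.** None was found.

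- The risk table under Safety considerations covers saliva aspiration during device use, gum or jaw discomfort, and infection control. It has no row for the swallow tests.
- The discontinuation rule refers to an AE or, as an alternative, a medical condition. The protocol therefore recognises untoward conditions that are not AEs.
- Data monitoring for safety includes the assessments, while the AE definition does not reach harm caused by them. Monitoring scope and definition do not match.

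**Step 4: size.** The protocol gives no event rate and no proportion attributed to the device. Purely as illustration, suppose 5 of 50 residents (50 being the recruitment ceiling) had a non-serious chest infection. The all-cause figure would be 5/50 = 10% (exact 95% interval 3.3% to 21.8%). If 0 to 5 of them were attributed to the device, the figure under the protocol's definition could be anything from 0/50 = 0% (two-sided 95% upper limit 7.1%) to 5/50 = 10%. With 1 attributed it would be 1/50 = 2% (0.05% to 10.6%). The range shows that the recorded figure depends on an unspecified judgement. It says nothing about what will happen in this study.

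**The case against.** The strongest reply is that the protocol has other nets. The SAE line lists death and hospitalisation without a causal condition, and only its life-threatening item refers back to AEs. The UE line has no causal condition either. The water test records signs of choking as part of its outcome, and a qualified speech pathologist carries out the assessments. The facility's incident system may capture far more than the AE definition requires. All of this stands, and it confines the point to non-serious events, to harm from the tests, and to the mismatch between the AE and SAE lines.

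It does not close the gap. UEs are limited to incidents that call the intervention protocol into question, and the facility's criteria are not given. An observation of choking in Table 1 is a test result. It does not become an AE, so the AE reporting times do not attach to it. For the solid-bolus test, Table 1 does not list choking as something to observe.

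Several stronger readings are tempting but unsupported.

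- *Care staff must decide causation before recording anything.* The protocol says only that they enter events under facility guidelines. The filter could equally apply later, at classification.
- *The principal investigator judges severity alone.* The risk matrix and the university's adverse events form are not shown, and either may already ask about relatedness.
- *Staff will usually blame existing dysphagia.* Nothing in the protocol says so.
- *The later trial would be planned on a false safety rate.* The Background and Study Design sections state other uses: acceptability, recruitment, retention and sample size.

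**Conclusion.** The point holds as a defect in a stated definition. Followed literally, the protocol does not count as AEs (a) non-serious events judged unrelated to the device, including chest infections managed without admission, or (b) harm from the swallow tests. The AE and SAE lines also pull in different directions on whether causation is required.

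The conclusion rests on reading intervention as the device programme, which is how the Study procedures subsection uses it, and on the absence of any wider definition elsewhere. A reader might infer that all chest infections, or all choking during tests, would go unrecorded. The protocol does not support that, because serious events and choking in the water test have other routes.

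The effect on event counts cannot be quantified from the protocol. That AEs are not listed under Study Outcomes is not part of the point: safety has its own subsections, and how events are tabulated can be left to an analysis plan.

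**What to change.** Make three changes before enrolment, since an event that never enters the study record may not be recoverable later.

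1. Define an AE as any untoward medical occurrence in an enrolled resident from the first study assessment up to and including the post-treatment assessment, whether or not thought related to the device or to a study test.
2. Have the principal investigator record relatedness as a separate judgement, once for the device and once for the study assessments.
3. Bring the SAE and UE lines into agreement with that definition, so that seriousness and unexpectedness are properties of an AE and none of the three depends on prior attribution.

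The cost is a change of wording and, if the existing form does not already hold them, two relatedness entries. The real downside is workload: more minor, unrelated events will be recorded in a frail population. No change to the device schedule, the assessments or clinical management is involved.
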